## Background

During the past 50 years, incisional and ventral hernia repair surgery has evolved from direct suture repair to the use of synthetic mesh to obtain a tension-free repair [1–3]. Finally, the tension-free concepts have been applied to laparoscopic surgery. Laparoscopic repair of incisional/ventral hernias (LIVHR) has gained increasing popularity, since many studies, included three meta-analyses, have reported encouraging results in terms of wound infection, hospital stay and post-operative pain, and recurrence rates comparable with the open approach [1–8].

Besides patient selection (age, sex, comorbidities, obesity, hernia site and size, eventual recurrence and type of previous abdominal surgery) and patient compliance, the choice of the mesh (bio-materials, size and shape) and fixation methods (titanium tacks, absorbable tacks, fibrin glue) are considered crucial issues to achieve optimal results and reduce complication and recurrence rates [4,5,9–12]. Lightweight meshes are often considered the first choice for hernia repair by many authors, since the evidence that the decreased density of the non-absorbable material could reduce the “foreign-body response,” improve abdominal wall compliance, cause less shrinkage and enhance the integration in host tissues [13–15]. Titanium helicoidal tacks are still considered the “gold standard” for mesh fixation [16–20]. However, several complications caused by these tacks have been reported (adhesion formation and bowel perforation). Furthermore, these devices may be involved in the genesis of some post-operative pain. Recently, absorbable tacks have been introduced [21] in combination with lightweight meshes, under the assumption that permanent fixation is no longer needed after the mesh is integrated within host tissues, potentially avoiding some of the above-described tack-related complications. Nevertheless, the efficacy of the use of absorbable tacks has never been compared to titanium tacks in a prospective analysis: only a few observational studies report similar results during a mid-term post-operative follow-up [21–23].

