### Randomization, allocation concealment, and blinding

A simple 1:1 allocation ratio randomization (without any restriction) will be guaranteed by an on-line computerized random generator. Patients will be randomly assigned to either Group A or Group B in the operating room, just before surgery.

Patients will be kept blind to the allocation status. Furthermore, post-operative controls will be performed at each center by a physician not directly involved in the study. He will be kept blind to the particular device used on each patient. Due to the nature of the intervention, the operating staff cannot be blinded to allocation but will be instructed not to disclose the allocation status of the participant at any time.

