### Intervention, preoperative and post-operative management

All patients will be assessed preoperatively by clinical examination and abdominal computed tomography (CT) or ultrasound (US) scan to evaluate the size and number of the defect(s).

The devices used in the study (meshes and tacks) will be:Physiomesh™ (Ethicon Endo-Surgery, Johnson & Johnson, Inc.), a lightweight polypropylene mesh with double face absorbable layer engineered to be placed on the peritoneal surfaceProtack™ (Covidien Surgical, Mansfield, MA, USA), permanent titanium helicoidal tacksSecurestrap™ (Ethicon Endo-Surgery, Johnson & Johnson, Inc.), “U”-shaped absorbable tacks made by polydioxanone, completely resorbed by hydrolysis within 12–18 months after implantation

All the procedures will be carried out using the same surgical technique, already described in previous studies [22,23]. In particular, there will be careful adhesiolysis of the entire abdominal wall, a search for additional defects, overlapping the defect for at least 3 cm on each side, setting the tacks at the distance of 1.5 cm in a double crown configuration [31] and no use of transfixed sutures or glue. After surgery, compressive dressing will be placed for 4 weeks.

Each surgeon will be provided with a precise description of the standardized technique and a checklist of the aforementioned necessary technical items to be controlled, filled for every patient and turned back to the Reference Center. Adherence to the protocol will be assessed by review of the procedure videos: all centers will share the videos with the Reference Center. The operations performed by the Reference Center will be examined by the primary surgeon of another participating center who will check that all items on the checklist have been correctly performed.

A member of the operating team will note the patients and intervention characteristics in an online database including the following parameters:Patient characteristics (sex, age, comorbidities, personal therapy)Hernia features (location and size)Mesh sizeType of tacks (absorbable/non-absorbable)Number of tacks usedOperating timePost-operative hospital stay

Post-operative complications during the index admission (according to the Clavien-Dindo classification) [32].

Acute post-operative pain (using the Visual Numeric Scale (VNS) for pain classification) [33].

Pain management (use of analgesic drugs).

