### Statistical methods

The sample size calculation is based on the primary end point. A sample size of 110 in each group permits the achievement of a study power of 80 %, to detect a non-inferiority margin difference between the devices used. The reference group proportion is 0.07. The treatment group proportion is assumed to be 0.13 under the null hypothesis of inferiority. The statistic test used will be the one-sided Z test (unpooled). The significance level of the test will be targeted at 0.05.

The same sample size will also be adequate to evaluate the secondary endpoints.

Statistical analysis will be performed at 1, 2 and 3 years after the first patient’s enrollment by a statistician affiliated with the Reference Center.

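### The stated primary test is unadjusted although allocation is unrestricted and hernia size is recorded before surgery; a pre-specified size-stratified risk difference would be a small, conditional improvement

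*Protocol article*

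**What the plan says.** - **Primary test** (Statistical methods): "The statistic test used will be the one-sided Z test (unpooled". No covariate or stratum is named. The level is given as "The significance level of the test will be targeted at 0.05".
- **Margin** (same section): "The reference group proportion is 0.07" and "The treatment group proportion is assumed to be 0.13 under the null hypothesis of inferiority", which implies 0.13 − 0.07 = 0.06, or 6 percentage points.
- **Allocation** (Randomization, allocation concealment, and blinding): "A simple 1:1 allocation ratio randomization (without any restriction". There is no blocking and no stratification by center or hernia type.
- **Size is available** (Intervention, preoperative and post-operative management): every patient has a clinical examination and a CT or ultrasound scan before surgery to assess the size and number of defects. The online database includes "Hernia features (location and size".
- **Size as a patient factor** (Background): it is one entry in a list of patient-selection factors, among them "obesity, hernia site and size, eventual recurrence and type of previous abdominal surgery". That list stands beside the choice of mesh and fixation, and it is that choice which the sentence calls crucial.

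**The concern.** If large hernias recur more often than small ones, a chance surplus of large hernias in one arm moves the crude difference for reasons unrelated to the tack. Simple randomization of 220 patients does nothing to limit such a surplus, and the named test does nothing to remove it. The whole non-inferiority claim turns on 6 points, so a shift of a point or more matters. If an imbalance appears once the data are unblinded, any adjustment will be post hoc and open to dispute. Naming the adjustment beforehand avoids that, and the covariate is already collected.

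**Working it through.** **Inputs from the protocol article.** 110 per arm, control rate 0.07, implied margin 0.06, one-sided level 0.05, unpooled variance, simple 1:1 allocation.

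**Assumed, because the documents give no figure.** 30% of hernias are large, overall recurrence is 7% in both arms, and the large-to-small risk ratio is 1, 2, 3.5 or 7. The corresponding recurrence risks (large v small) are 7% v 7%, 10.8% v 5.4%, 14% v 4% and 17.5% v 2.5%. Each pair averages to 7%; for example 0.3 × 14 + 0.7 × 4 = 7.

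**Step 1: the plan's own figure.** The article says: "A sample size of 110 in each group permits the achievement of a study power of 80" (per cent). With equal true rates:
- SE = √(2 × 0.07 × 0.93 / 110) = 0.0344
- power = Φ(0.06/0.0344 − 1.645) = Φ(0.099) = 54.0%

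The stated 80% is not reproduced; it would need 224 per arm. That is a separate matter, and 54% is only the baseline here.

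**Step 2: size of a chance imbalance.** The SD of the between-arm difference in the share of large hernias is √(0.3 × 0.7 × 2/110) = 6.2 points. The shift in the crude difference is this imbalance times the risk difference between size strata:

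| Risk ratio | Risk difference, large − small | Shift at 1 SD | Shift at 2 SD | 2-SD shift as share of margin |
|---|---|---|---|---|
| 1 | 0 | 0 | 0 | 0% |
| 2 | 5.4 points | 0.3 | 0.7 | 11% |
| 3.5 | 10 points | 0.6 | 1.2 | 21% |
| 7 | 15 points | 0.9 | 1.9 | 31% |

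**Step 3: gain from stratifying, by formula.** Stratification removes the between-stratum part of the variance, 0.3 × 0.7 × (risk difference)², from p(1 − p) = 0.0651.
- Ratio 2: 0.0006/0.0651 = 0.9% less variance; power 54.3%
- Ratio 3.5: 0.0021/0.0651 = 3.2%; SE = √(2 × 0.0630/110) = 0.0338; power 55.1%
- Ratio 7: 0.0047/0.0651 = 7.3%; SE = √(2 × 0.0604/110) = 0.0331; power 56.6%

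**Step 4: check by simulation with the actual sparse counts.** 220 patients, simple randomization, unpooled Z test against the Mantel-Haenszel risk difference with Sato variance, 200,000 trials per scenario. Crude power is about 55%, slightly above the formula.

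| Risk ratio | Gain in power at equal true rates |
|---|---|
| 1 | 0 points |
| 2 | 0.3 |
| 3.5 | 1.2 |
| 7 | 2.8 |

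When the absorbable tack is truly 6 points worse, false non-inferiority is 5.6–5.7% with either method. If size is not prognostic, the variance of the stratified estimate is about 0.5% higher than that of the crude one.

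**Step 5: trials that happen to be imbalanced.** With 30% large, about 7% of trials have 9 to 20 points fewer large hernias in the absorbable arm. In those trials, when the absorbable tack is truly 6 points worse, the crude test declares non-inferiority in 9.3% (ratio 3.5) to 11.6% (ratio 7); the stratified test does so in 5.6–5.8%. In the mirror case with equal true rates, crude power falls to 41% or 35%, while stratified power stays at 55–58%.

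**The case against.** The strongest reply is that nothing here is wrong. An unpooled two-proportion test is valid under simple randomization, and its standard error already covers chance imbalance in size. The shifts in the table run in either direction and are not error on top of that standard error. This stands: a reader might infer that unrestricted allocation biases the test, and the documents do not support that. Step 5 describes a subset of trials, not the average.

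A reader might also infer that the protocol singles out size as crucial for recurrence. It does not. Size is one item among several patient factors, with no effect quantified, no cut-off and no share of large hernias. The choice of size over obesity or previous recurrence is therefore a judgement. Its support is that size is objective and measured on imaging before surgery.

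The sentence on the test stands among the sample-size inputs, and an unseen analysis plan may add adjusted analyses. That is possible. Still, it is the only test the article names for the primary endpoint, and the suggestion concerns that stated choice, not an omission.

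The objection that about 15 recurrences (220 × 0.07 = 15.4) are too few for adjustment does not stand for this method. It applies to regression with several covariates. A two-stratum Mantel-Haenszel difference estimates no covariate coefficient, and the simulation shows error control matching the crude test at these counts.

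Finally, the change is not free. The cut-off is a new choice, operating staff know the allocation, and tack type is in the database. Enrollment began on 1 June 2014 and the article appeared on 4 June 2015, so the first yearly analysis was already due. A cut-off chosen after outcomes have been seen by arm could look data-driven. This also stands, and it limits when the change can be made.

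**Conclusion.** The point holds as an optional improvement of low severity. The stated primary test leaves unused a baseline variable that the trial already collects, under an allocation scheme that does not balance it. Stratifying by preoperative size protects against chance imbalance on the same 6-point scale. The average gain in power is 0 to 2.8 points over risk ratios of 1 to 7, and only about 0.3 points at a ratio of 2. These figures rest on the assumed 30% share of large hernias and 7% overall recurrence; neither the share nor the size effect is in the documents.

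A reader might infer that stratification rescues an underpowered trial. It does not: even at a ratio of 7 the formula gives 56.6%, far from 80%.

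**What to change.** Add a sentence to the protocol or analysis plan. The primary estimate is the Mantel-Haenszel risk difference in 3-year recurrence, stratified by preoperative hernia size in two categories, with Sato variance. Non-inferiority is concluded if the upper one-sided 95% limit lies below 6 points. Keep the unpooled Z test as a sensitivity analysis.

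State the cut-off, say that size is the preoperative imaging measurement, and say how patients with several defects are classified. Fix all of this before any outcome analysis by arm, including the 1-year and 2-year evaluations. If outcomes by arm have already been examined, keep the unadjusted test as primary and report the stratified estimate as supportive.

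Cost: no extra patients or data, one decision on the cut-off, and a variance about 0.5% higher if size turns out not to be prognostic.

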## Abstract

**Background:**

Laparoscopic repair of ventral and incisional hernias has gained popularity since many studies have reported encouraging results in terms of outcomee and recurrence. Choice of mesh and fixation methods are considered crucial issues in preventing recurrences and complications. Lightweight meshes are considered the first choice due to their biomechanical properties and the ability to integrate into the abdominal wall. Titanium helicoidal tacks still represent the “gold standard” for mesh fixation, even if they have been suggested to be involved in the genesis of post-operative pain and complications. Recently, absorbable tacks have been introduced, under the hypothesis that there will be no need to maintain a permanent fixation device after mesh integration. Nevertheless, there is no evidence that absorbable tacks may guarantee the same results as titanium tacks in terms of strength of fixation and recurrence rates. The primary end point of the present trial is to test the hypothesis that absorbable tacks are non-inferior to titanium tacks in laparoscopic incisional and ventral hernia repair (LIVHR) by lightweight polypropylene mesh, in terms of recurrence rates at 3-year follow-up. Surgical complications, post-operative stay, comfort and pain are secondary end points to be assessed.

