### Study population and eligibility criteria

All consecutive patients referred to the involved surgical units will be checked to determine eligibility, by one dedicated team member, according to the inclusion and exclusion criteria specified in an additional file (see Additional file 1).

All the eligible patients will be consecutively enrolled in the study until the sample size of 220 patients is reached. The included patients will be divided into two groups:Group A: patients submitted to LIVHR by lightweight polypropylene mesh fixed by titanium helicoidal tacks (control group);Group B: patients submitted to LIVHR by lightweight polypropylene mesh fixed by absorbable tacks (study group).

Each patient will be introduced to the trial by a member of the research group and receive an explanation of the study protocol (including random assignment of the fixation device that will be used during surgery). A specific informed consent regarding participation in the trial, randomization and explanation of the laparoscopic hernia repair, with no disclosure about the fixation device will be obtained and signed before enrolling in the study.

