There will be no difference in preoperative or post-operative care between the two groups. All patients will receive 1 dose (1 g) of paracetamol given intravenously at surgery and 2 more, each at 8-hour interval. Additional need for pain management will be noted on the records. The follow-up will be scheduled as follows:1 week (clinical evaluation)4 weeks (clinical evaluation)6 months (clinical evaluation or phone interview)12 months (phone call and eventual clinical evaluation)24 months after surgery (phone call and eventual clinical evaluation)36 months after surgery (phone call and eventual clinical evaluation)

During the follow-up, hernia recurrence (with eventual imaging studies) and post-operative complications will be checked. The following data will be also evaluated, using the licensed Carolinas Comfort Scale (CCS) [34,35]:Pain (during resting, during daily activities, during walking, during exercise):Pain control by use of analgesic drugs (which kind of drug, which dosage)Pain at physical examination

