### Outcome parameters

The primary end point of the study is:comparison of the results of the use of metallic and absorbable tacks to fix lightweight polypropylene meshes during LIVHR, in terms of hernia recurrence, to test the hypothesis of non-inferiority of absorbable tacks when compared to titanium tacks.

The endpoint will be measured by the recurrence rate at 3 years; interim evaluations will be done at 1-year and 2-year follow-up.

The secondary end point is:comparison of intraoperative and early post-operative outcomes, in terms of surgical complications, post-operative stay, comfort and pain

The comfort and pain parameters will be measured using the licensed CC S; surgical complications will be evaluated by the Clavien-Dindo classification [32] and on the basis of reoperation and readmission rates (1–2 and 3 years).

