### Trial status

Patient enrollment started on 1 June 2014 after tEthical Committee approval.

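### Analysis dates counted from the first patient's enrollment contradict a primary endpoint of recurrence at 3 years of each patient's own follow-up

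*Protocol article*

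**What the plan says.** All references are to the protocol article.

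- **Statistical methods** sets the analysis dates: "Statistical analysis will be performed at 1, 2 and 3 years after the first patient’s enrollment". No later final analysis is mentioned. The test is a one-sided unpooled Z test at 0.05 with 110 patients per group. The reference proportion is 0.07 and the treatment proportion under the null is 0.13, so the implied margin is 0.13 − 0.07 = 0.06.
- **Outcome parameters** sets the endpoint and the interim looks: "The endpoint will be measured by the recurrence rate at 3 years; interim evaluations will be done at 1-year and 2-year follow-up".
- **Abstract (Background)** states the non-inferiority hypothesis "in terms of recurrence rates at 3-year follow-up". The main Background section also gives a 3-year follow-up for the primary objective.
- **Intervention, preoperative and post-operative management** starts the follow-up clock at each patient's operation. The last contact is listed as "36 months after surgery (phone call and eventual clinical evaluation").
- **Study population and eligibility criteria** makes entry staggered: "All the eligible patients will be consecutively enrolled in the study until the sample size of 220 patients is reached".
- **Trial status** gives the start of accrual, "Patient enrollment started on 1 June 2014", but no planned end or duration.

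**The concern.** Two clocks are in use. The endpoint and the visit schedule run from each patient's surgery. The analysis dates run from one calendar point, the first enrollment. With consecutive entry, a patient who enters *u* years after the first has only 3 − *u* years of follow-up at the third date. Even the first patient's 36-month contact falls on or after that date, because it is counted from surgery. The same mismatch affects the 1- and 2-year looks.

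In a superiority trial, analyzing early mostly costs power. In a non-inferiority trial with a fixed absolute margin it can do worse. If patients with short follow-up count as recurrence-free, both cumulative rates are too low, the difference between them narrows, and the margin does not narrow with it. An inferior device then passes more often than the nominal 5%.

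**Working it through.** **Inputs from Statistical methods.** n = 110 per arm, 3-year rates 0.07 and 0.13 at the null, margin 0.06, one-sided alpha 0.05 (z = 1.645), unpooled standard error.

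**Assumptions, because the documents give no figure.** Accrual is uniform over *A* years. Data are cut 3 years after first entry. Every patient stays in the denominator, and recurrences to date form the numerator.

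**Step 1: the nominal error rate.** With full follow-up the expected difference is 0.13 − 0.07 = 0.06, equal to the margin, so P(declare non-inferiority) = Φ(0 − 1.645) = 0.050. The planned 5% is reproduced. (The stated 110 per group is a separate matter. With equal true rates of 0.07, n = 2·0.07·0.93·(1.645 + 0.842)²/0.06² ≈ 224 per group. That does not affect the timing point.)

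**Step 2: follow-up at the third date.** Mean follow-up is 36 − (accrual months)/2, which is 33, 30 or 24 months for accrual over 6, 12 or 24 months. The share of patients within one month of the 36-month visit is 1/6 = 17%, 1/12 = 8% or 1/24 = 4%. Out of 220 that is about 37, 18 or 9 patients.

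**Step 3: crude rates under constant hazards.** The yearly hazards are −ln(0.93)/3 = 0.02419 and −ln(0.87)/3 = 0.04642. Averaged over follow-up from 3 − *A* to 3 years, the expected proportion is

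1 − [exp(−λ(3 − A)) − exp(−3λ)]/(λA).

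For A = 1:
- control: 1 − (0.95277 − 0.93)/0.02419 = 0.0587
- absorbable: 1 − (0.91134 − 0.87)/0.04642 = 0.1095

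**Step 4: false non-inferiority rate.** P = Φ((0.06 − difference)/SE − 1.645), with SE = √[(p₁(1 − p₁) + p₂(1 − p₂))/110]. For A = 1, SE = 0.0373 and P = Φ(0.246 − 1.645) = 0.081.

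| Accrual | Control | Absorbable | Difference | SE | P |
|---|---|---|---|---|---|
| none (full follow-up) | 0.070 | 0.130 | 0.060 | 0.0402 | 0.050 |
| 6 months | 0.0644 | 0.1198 | 0.0555 | 0.0388 | 0.063 |
| 12 months | 0.0587 | 0.1095 | 0.0508 | 0.0373 | 0.081 |
| 18 months | 0.0529 | 0.0990 | 0.0461 | 0.0356 | 0.105 |
| 24 months | 0.0471 | 0.0883 | 0.0412 | 0.0338 | 0.138 |

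Exact binomial enumeration gives 0.055 with full follow-up, 0.089 for 12 months and 0.156 for 24 months, so the pattern does not come from the normal approximation.

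**Step 5: other recurrence patterns, same 3-year rates.**

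| Pattern | 6 months | 12 months | 24 months |
|---|---|---|---|
| Concentrated early: F(t) = 1 − (1 − p)^√(t/3) | 0.056 | 0.064 | 0.088 |
| Constant hazard | 0.063 | 0.081 | 0.138 |
| Excess only after year 1: equal hazards to month 12, then (0.13926 − 0.02419)/2 = 0.0575 per year in the absorbable arm | 0.072 | 0.104 | 0.227 |

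Every case lies above 0.050.

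**Step 6: other ways to handle incomplete follow-up.** Restricting the test to patients with 36 months removes this bias, but Step 2 shows that almost no one would be left. A time-to-event estimate would use the partial follow-up properly, but very few patients would be at risk at 3 years, and it is not the stated test.

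**The case against.** The strongest reply is that only one sentence uses a first-patient clock. The Abstract, Background, visit schedule and Outcome parameters all point to per-patient follow-up, and the interim looks are described by follow-up time. The sentence may simply be loose wording for a yearly reporting schedule. This stands in part: a reader might infer a settled plan to test the 3-year endpoint on immature data, and the documents do not show that. They show a contradiction. It still has to be resolved, because the sentence is the only explicit analysis date.

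A reader might also infer that the timing in itself biases the test toward non-inferiority. That is too strong. The bias arises only if patients short of 36 months are counted as not recurred. The stated test and group size make that plausible, but the protocol does not say it.

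The size may also be small. There are five units, and each surgeon is said to do more than fifty procedures a year with these devices. With at least one surgeon per unit, that is more than 5 × 50 = 250 a year against a target of 220. Not all patients would be eligible or consent, so this does not establish accrual speed, but short accrual belongs in the range. At 6 months the inflation is modest.

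Finally, because the absorbable tacks are "completely resorbed by hydrolysis within 12–18 months after implantation", it is tempting to say that the lost months are those in which excess recurrences are expected. No passage says so. The Discussion argues that integrated lightweight mesh may not need permanent fixation. With 12-month accrual every patient would also have about 24 months of follow-up at the cut, beyond that window.

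**Conclusion.** The analysis dates are wrong as written: they cannot deliver the 3-year endpoint, however fast patients are recruited. That conclusion needs no assumption beyond staggered entry.

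The effect on the test is conditional. It requires that the date is followed literally and that crude proportions are compared with all 110 per arm in the denominator. With a true 7% versus 13% at 3 years and uniform accrual, the false non-inferiority rate is then about 6%, 8% or 14% for 6, 12 or 24 months under constant hazard, instead of 5%. Across recurrence patterns and 6 to 24 months of accrual, the range is about 5.6% to 23%. The upper end assumes that the excess arises only after year 1, which the documents do not support. Under the other ways of handling incomplete follow-up the problem is too little information at 3 years, not this bias.

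**What to change.** Replace the timing sentence in Statistical methods with: *The primary analysis will be performed once the last randomized patient has completed the 36-month assessment (or has died, withdrawn or been lost).* Tie the 1- and 2-year evaluations to each patient's own 12- and 24-month follow-up, so that Statistical methods agrees with Outcome parameters and the visit schedule.

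The visits to 36 months are already scheduled, so data collection and design do not change. The cost is that the final report comes later by the length of the accrual period.
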